## Abstract

**Background:**

Working during the night interferes with the timing of normal daily activities and is associated with an increased risk of chronic diseases. Under controlled experimental conditions, interventions focusing on sleep and nutrition can mitigate the short-term adverse effects of shift work. However, it is unclear how these results translate to real-life, how they can be targeted to individual conditions, and how they relate to long-term health. Therefore, the current study aims to implement a personalized sleep and nutritional intervention among night shift workers in the field.

**Methods:**

A non-blinded controlled intervention study is used, consisting of a run-in period, an intervention of 3 months, post-intervention measurements, and a follow-up after 12 months. Three study arms are included: sleep intervention, nutritional intervention, and control group (*n* = 25 each). Participants are healthy 18–60-year male night shift workers, with at least one year of experience in night shift work. Information from the run-in period will be used to personalize the interventions. The main outcomes are sleep measurements and continuous interstitial glucose levels. Furthermore, general health biomarkers and parameters will be determined to further evaluate effects on long-term health.

**Discussion:**

This study aims to mitigate negative health consequences associated with night shift work by introducing two personalized preventive interventions. If proven effective, the personalized interventions may serve as practical solutions that can have a meaningful impact on the sustainable health and employability of night shift workers. This study will thereby contribute to the current need for high–quality data on preventative strategies for night shift work in a real-life context.

**Trial registration:**

This trial has been registered under ClinicalTrials.gov Identifier NCT06147089. Registered 27 November 2023.

## Introduction

Working during the night is associated with detrimental health effects such as increased risk of cardiovascular diseases, type 2 diabetes, respiratory infections, and cancer [1, 2]. Surveys estimate that approximately 19% of the workers in the European Union (EU) work during the night at least once per month [3], placing a considerable segment of the workforce at increased disease risk.

A widely supported hypothesis is that the misalignment between the endogenous circadian (i.e., near-24-h) rhythms and the timing of the sleep–wake cycle underlies the negative health effects associated with night shift work [4]. For example, the circadian system increases alertness during the daytime and decreases wakefulness during the nighttime [5]. This process is augmented by a homeostatic pressure for sleep, which builds across waking hours [6]. Normally, these two processes function in synchrony with the environmental light/dark cycle to maintain alertness while at work and sleep during the night. In contrast, night shift workers must work and sleep at times that conflict with their circadian rhythms.

Due to this altered sleep–wake cycle, eating, and activity, night shift work can lead to changes in physiology. For example shorter, less consolidated, and highly disrupted sleep has been observed in night shift workers during the day, while increased sleepiness and performance decrements are observed during night shifts [7]. Similarly, eating out of synchrony with the endogenous biological clock can lead to metabolic health problems, including alterations in glucose homeostasis such as tissue-specific insulin resistance [8, 9]. Furthermore, higher postprandial glucose concentrations may occur when eating during the night, in comparison to eating during the day [10].

As diet and sleep behavior are modifiable, it is important to understand how these factors might mediate the relationship between night shift work and health and how they can be implemented as countermeasures. Recent research shows promising results, as illustrated by the beneficial effect on cognitive performance and sleep duration around night shifts of power naps [11, 12] or limiting prior wakefulness (i.e. cumulative duration of wakefulness) [13]. Multiple sleep episodes can be as recuperative as a consolidated sleep episode [14–16]. As sleep insufficiency is the most widespread problem affecting night and rotating shift workers [17, 18], these strategies may be one way of minimizing overall daily sleep loss and associated declines in cardiovascular and metabolic health [19, 20]. Behavioral interventions focused on timing of nutrition mitigated the adverse effects in glucose regulation induced by a disrupted sleep–wake schedule [21, 22]. Furthermore, consuming a small meal during the night shift attenuates the increase in sleepiness and the decrease in vigor across the night shift, relative to consuming a larger meal or not eating during the night [23].

However, the limitation of these studies is that they focused only on short-term health effects such as fatigue and sleep [24], while evidence-based measures to minimize long-term health risks are currently lacking [25]. Furthermore, it is unclear how results obtained under controlled experimental conditions can be generalized to predict health effects in night shift workers in real-life [26, 27].

The adoption of a personalized approach may be a useful strategy to maximize health benefits in the field. Personalized interventions use individual-specific information to promote beneficial behavior change [28]. The personalized design results in greater dietary improvement compared to generic advice [29]. Furthermore, often a high degree of inter-individual metabolic responses to food intake is observed, as well as inter-individual differences in sleep responses to night shift work [30–32]. Accordingly, tailoring advice (based on objective data, as well as social context) may increase suitability of an intervention for each individual.

In summary, there is currently limited evidence on effective interventions in a real-life context to minimize short- as well as long-term health consequences of night shift work. As shift work is prevalent and difficult to limit in many job types, research into preventative interventions for night shift workers is an important avenue of investigation. Therefore, the current protocol describes a sleep or nutritional personalized intervention for night shift workers in a real-life. Our hypotheses are two-fold: i) the personalized sleep intervention can improve sleep duration and sleep quality in the field, particularly after night shifts, and ii) the personalized nutritional intervention can improve glucose metabolism in night shift workers. We expect both interventions to increase alertness, while decreasing fatigue during night shifts, in real life. If proven effective, the personalized interventions may serve as practical solutions that can have a meaningful impact on both short- and long-term health of night shift workers.

## Methods

### Study design

A non-blinded controlled intervention study will be used to investigate the effect of a personalized sleep or nutritional intervention. The study will include a run-in period with baseline levels, a 3-month intervention with measurements at the start of the intervention, post-intervention measurements immediately following the intervention, and a follow-up after 12 months. There are three study arms: control group (no advice), personalized sleep intervention (SL), and personalized nutritional intervention (NU). During the run-in period the following will be measured: sleep, physical activity, food intake, and glucose levels by continuous glucose monitoring (CGM) during 14 days covering night shifts, rest days, and non-night shifts. Information from this baseline will be used for the subsequent personalized advice. The intervention entails following the personalized advice for a period of three months.

The groups will be open-labeled. The intervention involves observable behavioral changes, of which the participants will be aware themselves. This makes it difficult to conceal whether a participant is receiving the intervention or not. Participants will have the opportunity to select their preferred intervention. This approach was chosen to optimize motivation for participants to adhere to the personalized intervention.

The study has been approved by the Medical Ethical Review Committee of the Erasmus University Medical Center (Erasmus MC) and registered (27 November 2023) under ClinicalTrials.gov identifier NCT06147089. Participant recruitment is ongoing at the time of submission. An overview of the study setup is depicted in Fig. 1.

**Fig. 1 Fig1:**
[figure not shown]
Schematic overview of the study. White represents measurements that will be gathered during a study visit. Green indicates measurements that will be taken during the 14-day period (covering night shifts, rest days, and non-night shifts) and monitored remotely. Grey indicates online measurements taken outside of a study visit. The follow-up occurs 12 months after the baseline visit. NU = nutritional intervention

### Study population

The study population will consist of male employees who work at least 4 night shifts a month on average, with at least 1 year prior experience with shift work. Participants work in shifts with a duration of 6 h-12 h. A shift is categorized as a night shift if at least 1 h of working falls between midnight (00:00) and 06:00 in the morning. Participants can work night shifts only or work on rotating shifts. Participants are 18 to 60 years of age and without a diagnosis of a major disease. All participants live or work in the Netherlands and speak Dutch natively or fluently. The aim is to include 25 participants in each arm of the study.

### Sample size calculations

Sample size calculations were employed in GLIMMPSE 3.0, a validated manualized sample size calculator for longitudinal designs [33, 34]. We performed a repeated measure analysis sample size calculation using the Hotteling-Lawley Trace statistic to test for a time-by-treatment interaction effect, aiming for a power of 0.80 and a Type I error rate of 0.05.

For sleep outcomes, we predict a standard deviation of 84.4 min for total sleep time (TST), based on a laboratory study [35] comparing a control group with a sleep intervention. These estimates are based on large effect sizes, and it is unclear how these scores translate to a field study, therefore a mean scale factor was included to account for alternative values. Furthermore, we assumed that the Pearson correlation between all time-points was relatively stable at 0.48 based on a study on TST with a 2-year interval [36] and preliminary data from an Erasmus MC study on sleep and corona vaccination in shift workers (unpublished data, for protocol, see S-CORE study [37]). Taken together, for a desired power of 0.80 and a Type I error rate of 0.05, we estimated that we would need 18 participants per group for a difference of 128 min in TST as the main outcome in the sleep intervention arm.

Due to the paucity of previous data on continuous glucose levels of shift workers, there is no clear notion of the expected variability in a representative population sample. However, there is one observational study [38] that compared 62 daytime workers to 62 night shift workers who wore a continuous glucose monitor for 3–7 days, which showed standard deviation of 0.49 mmol/L for a mean nighttime glucose of 5.32 [38]. We assumed Pearson correlations of 0.85 between T0 and T1 and 0.71 between T1 and T2, considering patterns observed in Type I diabetes patients [39]. With these assumptions, we calculated a required sample size of 25 participants per group for a difference of 0.23 mmol/L in continuous glucose measurements as main outcome in the nutritional intervention. In total, considering both CGM and TST, our required sample size is *N* = 25 per group.

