### Statistical analysis

Our primary analysis will assess the changes over time (pre- and post-intervention) in sleep quantity, sleep quality and glucose regulation. The intra-individual differences within the NU and the SL group will be compared to the control group. By considering the intra-individual differences, participants can serve as their own controls, increasing the sensitivity of the analysis to potentially smaller changes.

Linear and logistic mixed models will be employed using statistical software (SPSS, R studio) to analyze the main effects over time for the factor condition (3 groups). A random intercept statement will account for inter-individual variations. Significance tests will be 2-tailed and at p ≤ 0.05. Covariates like age, sex, and BMI may be considered, and participants with baseline and at least one follow-up measurement will be included in the statistical analyses. Selective loss to follow-up will be analyzed through logistic regression. Covariates will be imputed using multiple imputation if needed.

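### The printed TST sample size does not match its own inputs: 128 min needs about 9 per group (8 to 13 over mean patterns), not 18

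*Protocol article*

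**What the plan says.** The Sample size calculations section describes a repeated-measures calculation, "using the Hotteling-Lawley Trace statistic to test for a time-by-treatment interaction effect". For TST it gives an SD of 84.4 min from a laboratory study and assumes that "the Pearson correlation between all time-points was relatively stable at 0.48". The stated target is "for a desired power of 0.80 and a Type I error rate of 0.05", and the Statistical analysis section adds "Significance tests will be 2-tailed and at p ≤ 0.05". The result is that "we estimated that we would need 18 participants per group for a difference of 128 min in TST".

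The same paragraph concedes that the laboratory effects are large and that "it is unclear how these scores translate to a field study, therefore a mean scale factor was included to account for alternative values". It gives neither the value of that factor nor the assumed means by arm and visit. The section then takes the larger of the TST and glucose requirements, which is 25 per group from the glucose calculation. Under Primary endpoints, actigraphic TST is collected at T0, T1 and T2 only; the 12-month follow-up has no actigraphy.

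**The concern.** A difference of 128 min against an SD of 84.4 min is about 1.5 SD (128 / 84.4 = 1.52). A two-group comparison of an effect that large at 80% power should need about 8 or 9 per group, so 18 stands out at once.

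TST is the outcome on which the sleep arm is sized, and actigraphic sleep is a primary endpoint. The authors themselves doubt that a laboratory effect carries over to the field. Anyone reading a modest or null result will want to know what difference the arm could have detected, and the printed sentence is the only guide. If its n and its difference do not belong together, it gives a false picture of the sensitivity.

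**Working it through.** **Inputs.** SD 84.4 min, r = 0.48 for all pairs of visits, power 0.80, alpha 0.05, difference 128 min, interaction test (all from Sample size calculations); two-sided testing (Statistical analysis); visits T0, T1, T2 (Primary endpoints). My assumption at this stage: 128 min is the between-group difference in change, unscaled, with a flat control arm.

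**Step 1: attempt to reproduce 18, two-group pre/post contrast.**
- SD of change = 84.4 × √(2 × (1 − 0.48)) = 84.4 × √1.04 = 86.07 min.
- Standardised difference = 128 / 86.07 = 1.487.
- Normal approximation: n = 2 × (1.960 + 0.842)² / 1.487² = 7.1, so 8 per group.
- Exact noncentral t: power is 0.790 at 8 per group, 0.842 at 9 and 0.991 at 18. The requirement is 9.

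The printed 18 is not reproduced.

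**Step 2: the Hotelling-Lawley interaction test, compound symmetry, r = 0.48.**

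| Groups and visits | Mean pattern (128 min at its largest) | n per group |
|---|---|---|
| 2 groups, 2 visits | pre/post | 9 |
| 2 groups, 3 visits | sustained, or last visit only | 9 |
| 2 groups, 3 visits | linear | 11 |
| 3 groups, 3 visits | sleep arm only, sustained | 8 |
| 3 groups, 3 visits | sleep arm only, linear | 10 |
| 3 groups, 3 visits | least favourable: linear, with half the effect in the nutrition arm | 13 |

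Simulation confirmed the two-group rows and the sustained and least favourable three-group rows. At 18 per group, power for 128 min is 0.99 for the pre/post contrast and 0.95 for the least favourable pattern.

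**Step 3: could another input account for the gap?**
- Setting the correlation to 0 in the pre/post contrast raises the requirement only to 15.
- With r kept at 0.48, the SD would have to be about 84.4 × 128 / 82.7 = 131 min.
- With two groups, alpha 0.025 gives 10 to 13 per group and power 0.90 gives 11 to 14.
- A fourth visit, which TST does not have, gives at most 15.

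**Step 4: what 18 per group does correspond to at 80% power.**
- Pre/post: 82.7 min, a scale of 82.7 / 128 = 0.65.
- Three visits, sustained: 80.8 min, scale 0.63.
- Three visits, linear: 93.3 min, scale 0.73.
- Over all patterns above: 78 to 103 min.

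**Step 5: what the planned 25 per group detects at 80% power.** Pre/post 69.6 min; sustained 67.6 min; linear 78.0 min; 65 to 86 min over patterns.

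**The case against.** The strongest reply is that the article mentions one further input, the mean scale factor, whose value an article may leave to the full protocol. With a factor of 0.75 and a linear effect over three visits in two groups, the requirement is exactly 18 per group (128 × 0.75 = 96 min). With 0.65 and a sustained effect it is also 18 (128 × 0.65 = 83.2 min). Alternatively, 128 min may be the change within the sleep arm. A control-arm change of 45 min then leaves a contrast of 128 − 45 = 83 min and again gives 18.

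This stands in part. The number 18 may be a correct software output, so a reader should not infer that the authors miscalculated by a factor of two. It does not rescue the sentence. Under each of these explanations the contrast tested with 80% power is roughly 80 to 100 min, while the text attaches 18 to 128 min. If 128 min is already the scaled between-group difference, 18 is about double what is needed. The conflict is between printed figures, which is more than a missing detail.

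A reader might also infer that 18 is the total of two arms of 9, reported as per group. The arithmetic fits (2 × 9 = 18), but nothing in the document says so, and it remains conjecture.

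Finally, 18 does not determine the trial's size, and the article already warns about large laboratory effects. Both points are fair and limit the weight of the finding.

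**Conclusion.** The pair of 18 per group and 128 min is inconsistent with the inputs printed in the same paragraph. Those inputs give about 9 per group, with a range of 8 to 13 over mean patterns. If 18 is right, the difference it belongs to is roughly 80 to 100 min. The documents do not show whether the scale factor, a control-arm change or a per-group/total mix-up lies behind it. The result rests on the printed SD, the common correlation of 0.48, complete data and equal arms.

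It would be tempting to conclude that the sleep arm is underpowered or that the trial is the wrong size. The documents do not support that. The error is conservative: 18 per group is more than enough for 128 min, and 25 per group is more still. The planned 25 comes from the glucose calculation and stays. What is misstated is the sensitivity of the sleep comparison, a worthwhile but inexpensive correction.

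**What to change.** Rerun the TST calculation and restate the sentence so that n and difference match. Give:

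- the mean scale factor, and whether 128 min is before or after scaling;
- the assumed means by arm and visit, including any change in the control arm;
- whether 18 is per group or a total.

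Then state the TST difference detectable with 80% power at the planned 25 per group under the chosen pattern. On the printed SD and correlation this is about 68 to 70 min for a pre/post or sustained effect, about 78 min for a linear effect, and 65 to 86 min over all patterns considered. No single replacement value should be printed until the authors confirm the pattern they used.

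The cost is one rerun and one reworded paragraph. The sample size, visits and analysis do not change.

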### Personalized intervention

At the personal advice meeting (Fig. 1), participants will receive verbal and written instructions on their sleep or nutritional advice. In addition to providing the participant with information, motivational interviewing technique will be applied to increase adherence to the advice. It is a one-on-one meeting, where participants have ample time to ask questions. The personalization will be based on the individual circumstances of the participant (work schedule, commuting time, familial or social obligations), as well as (bio)markers of sleep and metabolic health (Fig. 2). The personal advice meeting will not include blood samples, questionnaires or anthropometrics, in order to lessen the study burden for the participants.

**Fig. 2 Fig2:**
[figure not shown]
Baseline measurements are used to personalize the intervention. (1) Measurements collected during baseline, including sleep (via actigraphy watch, sleep diary, and sleep questionnaires), dietary behaviors (via food logging), and glucose metabolism (via continuous glucose monitoring and the Phenflex test with different blood based biomarkers measured pre- and postprandially). (2) These data and their interactions are visualized and analyzed to (3) personalize the sleep or nutritional advice

### Sleep intervention

The intervention will use multiple sleep episodes (split-sleep or naps) [11, 12], limiting prior wakefulness [13], and general guidelines on how to improve sleep for shift workers [40, 41], i.e. education on sleep hygiene, sleep and circadian pressure, planning of sleep, transitioning to day shifts/days off.

Baseline data from the run-in period will be used to generate personalized recommendations, including information on sleep quality and quantity (as measured by actigraphy and subjective questionnaire) and validated sleep questionnaires, like the Insomnia Severity Index (ISI) [42], Epworth Sleepiness Scale (ESS) [43], Pittsburgh Sleep Quality Index (PSQI) [44] and Shift Work Disorder questionnaire (SWD) [45]. These questionnaires can indicate a high vs. low-risk profile and differentiate for example between those who have trouble staying asleep vs. falling asleep. Lastly, social circumstances, as well as the opportunity to schedule extra sleep episodes within one’s schedule will be taken into account.

For instance, the tailored intervention can include using power naps during the night shift for those who have trouble staying awake during their night shift. Additionally, shift workers who wake up frequently, or have trouble falling back asleep, will be advised to wake up close to the start of their night shift to limit prior wakefulness.

### Nutritional intervention

The nutritional advice around nightshifts is built up in two steps. Firstly, advice on calorie distribution over 24 h will be provided. Specifically, participants will be advised to consume approximately 20% of their total daily caloric intake during a light midnight meal, 25% during breakfast (N.B. the end of the night shift but before sleep), 15% as an afternoon snack, and 40% during early dinner (early defined as 18:00–20:00 h) [23, 46]. Total daily caloric intake will be personalized based on individual estimated energy requirements [47].

Secondly, advice on macronutrient distribution over 24 h will be provided. Based on the fluctuations in insulin sensitivity throughout the day consumption of carbohydrates will be geared towards the morning, and fat intake towards the evening [23]. The advice entails that breakfast consists of 75% carbohydrates (CHO), 15% protein (PRO), and 10% fat (F), afternoon snack is 25% CHO, 25% PRO, 50% F, early dinner is 45% CHO, 20% PRO, 35% F, and light midnight meal is 55% CHO, 15% PRO, 30% F. Furthermore, overnight fasting and postprandial clinical biomarkers (i.e. the results of the PhenFlex Test and pre- and postprandial measurements of glucose, insulin, triglycerides, and cholesterol) will be used to personalize the advice related to intake of protein, carbohydrate and fat [48]. Advice on specific food products will also be provided, based on the outcomes of CGM and food logging. Lastly, personal dietary preferences will be taken into account (i.e. (dis)likes, halal, kosher).

